### Intervention

The intervention group will receive one SB capsule )600 mg( with breakfast for 60 days. The dosage of SB supplementation was determined, based on the previous study [22]. SB supplement (550 mg butyrate, 50 mg hydroxypropyl methylcellulose, medium-chain triglycerides (MCT), sodium hydroxide, and purified water) will be provided by Body Bio Company (Body Bio, USA). The control group will receive the same amount of placebo capsules for 60 days. Pharmacy Faculty of Tabriz University of Medical Sciences will provide placebo capsules (Tabriz, Iran, containing 600 mg of carboxymethyl cellulose). Size and color of SB capsules and placebo capsules are exactly similar. Both groups will receive SB and placebo capsules every 30 days. The remaining capsules returned by participants will be counted to determine adherence to the supplements in all patients. Adherence will be defined as consuming 90% of the supplements.

An expert dietician will design an individualized hypo-caloric diet for each participant. The Mifflin St. Jeor equation will be used to calculate total energy expenditure requirements [24]. Then, 500 kcals of the estimated energy needs will be deducted. The hypo-caloric diet composition will consist of 10–15% protein, 25–30% fat, and 55–60% carbohydrate. Compliance with diet will be checked weekly by phone calls as well as a 3-day food record at the onset and end-point of the study. Figure 3 depicts the schedule for the present study.

**Fig. 3 Fig3:**
[figure not shown]
SPIRIT figure: schedule for enrollment, intervention, and assessment

The research team will provide weekly communications via phone calls and messages to inform the participants about obesity, the current status of the study, and plans for the next phase, emphasizing study benefits as well as to acknowledge their support. In week 4, there will be a face-to-face session with the participant to assess anthropometric changes and help to maintain interest in study.

### Criteria for discontinuing or modifying allocated intervention

Since SB may affect the composition of the gut microbiota, temporary gastrointestinal symptoms such as bloating or diarrhea may occur. Taking the recommended daily dose regularly, gastrointestinal tolerance improves, and the symptoms usually disappear. However, the trial medication should be withdrawn from subjects reporting gastro-intestinal intolerance. This should be reported as an adverse event.

### Evaluation of diet, physical activity, and appetite

A checklist will be filled out at baseline, which includes demographic data and medical and drug history. For evaluation of dietary intake, the participants will be asked to keep a 3-day (one weekend and two weekdays) food record. Energy and nutrients analysis will be performed using Nutritionist IV (Hearst Corporation, USA). Physical activity level (PAL) will be calculated by the International Physical Activity Questionnaire short form (IPAQ-SF) [25]. To assess appetite, the participants will complete a visual analog scale (VAS) at baseline and end of study [26].

### Anthropometric assessments

Body weight will be measured for subjects wearing minimal clothing (Seca scale) and height will be measured by a wall-mounted meter. To calculate BMI, weight (kg) will be divided by height squared (m^2^). An accurate measurement of waist circumference (WC) will be taken, using a tape meter at the midpoint between the lowest rib and iliac crest at the end of normal expiration. Hip circumference (HC) will be measured at its widest point over the greatest trochanters. Waist/hip ratio (WHR) will also be calculated. Fat-free mass (FFM), FFM percent, fat-mass (FM), and FM percent, as well as visceral fat, will be estimated through MC-780 TANITA body composition analyzer (Tanita, Amsterdam, The Netherlands).

### Biochemical assays

Five milliliters of venous blood sample will be taken after a 12-h overnight fasting in vacuumed gel separator tubes at baseline and end of the study. Blood samples will be centrifuged at 3000 RPM for 5 min to extract the serum. Serum aliquots will be frozen (− 80 °C) to measure GLP1 (μg/mL) and insulin (μU/mL) using enzyme-linked immunosorbent assay (ELISA) kits.

Fasting blood sugar (FBS) (mg/dL), triglycerides (TG), total cholesterol (TC), high-density lipoprotein cholesterol (HDL-C), aspartate transaminase (AST), alanine transferase (ALT), and alkaline phosphatase (ALP) will be measured by enzymatic colorimetric kits. The Friedewald equation will be used to compute low-density lipoprotein cholesterol (LDL-C) concentrations. Calculation of the homeostatic model assessment for IR (HOMA-IR) will be done using the following formula: HOMA-IR = [fasting insulin (μIU/mL) × fasting glucose (mg/dL)]/405 [27].

### Gene expression assay

Five milliliters of blood samples will be collected in EDTA/K2 tubes. Peripheral blood mononuclear cells (PBMCs) will be isolated using Ficoll-Hypaque density gradient centrifugation. Total RNA extraction will be done using Trizol reagent, according the manufacturer’s instruction. After designing primers, the mRNA gene expression of PGC-1α, PPARα, and UCP1 genes will be applied using real-time polymerase chain reaction (real time-PCR). In real time-PCR tests, the housekeeping gene will be β-actin. The fold change of gene expressions will be calculated based on the Livak formula (2^–ΔΔCt^) [28].

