### Sample size

The sample size was estimated based on serum changes of GLP-1 [22], 95% confidence interval, and 80% power (two-sided *α* = 0.05 and *β* = 0.2) using sample size formula (Fig. 2) suggested for comparison of mean between the two groups when the endpoint is quantitative data in parallel designed RCTs. Furthermore, the means and standard deviation (SD) [23] of GLP-1 levels in the study mentioned above were as follows: Δμ = 17.84; SD1 = 17.93; and SD2 = 22.49. Lastly, considering a 20% dropout rate, 25 subjects were calculated for each group. Individuals who fulfilled the eligibility criteria will be included in the RCT.

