### Outcomes

Primary outcomes will be changes in means of anthropometrics indices, serum levels of GLP1, and fold change of PGC-1α, PPARα, and UCP1 genes between the control and intervention groups. Secondary outcomes are to compare the changes in means of lipid profile (serum levels of TG, TC, HDL-C, and LDL-C), FBS, fasting plasma insulin level, HOMA-IR, ALT, AST, and ALP between the control and intervention groups. All primary and secondary outcomes will be evaluated at the baseline and the end of the study (day 60 after intervention) for all participants. All outcomes and time points are specified in Fig. 3.

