### Statistical analysis

Data analysis of the present RCT will be conducted on an intention to treat (ITT) participants. ITT means outcome data obtained from all participants are included in the data analysis, regardless of protocol adherence. The data will be checked for accuracy and completeness at random intervals. The data will be expressed as means ± SD. For each variable, the percentage change will be calculated, as follows: [(E–B)/B ×100]; *E* is the end value, and *B* is the baseline value of the variable.

The Kolmogorov-Smirnov test will be used to examine the normality of the data. The intervention arm (SB) will be compared against the control (placebo) for all primary and secondary outcomes. The paired sample *t*-test and independent sample *t*-test will be performed for the comparison of parametric variables within and between groups, respectively. For non-parametric variables, the Mann-Whitney test and Wilcoxon signed rank test will be applied. Confounding factors including baseline values will be controlled using the analysis of covariance (ANCOVA) test. IBM SPSS software (version 21) (Armonk, NY, USA) will be used to analyze the data. A *P*-value less than 0.05 will be considered a statistically significant.

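### The three primary gene outcomes are fixed on the raw fold-change scale, so the mean ± SD summary and the baseline-adjusted ANCOVA are on a right-skewed scale; ΔCt would serve better

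*Protocol article*

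**What the plan says.** - **Scale.** Protocol article, Gene expression assay: "The fold change of gene expressions will be calculated based on" the Livak formula, 2^-ΔΔCt, with β-actin as the reference gene.
- **Role.** Protocol article, Outcomes: the primary outcomes include "fold change of PGC-1α, PPARα, and UCP1 genes between the control and intervention groups".
- **Summary.** Protocol article, Statistical analysis: "The data will be expressed as means ± SD". No geometric mean or median is offered.
- **Tests.** The same section checks normality by Kolmogorov-Smirnov. It uses t-tests for variables judged parametric and Mann-Whitney or Wilcoxon tests for the others. ANCOVA controls for confounders, including baseline values, and has no stated alternative for non-normal data.
- **Transformation.** The article mentions no log transformation and no analysis of ΔCt or ΔΔCt.
- **Sample size.** "The sample size was estimated based on serum changes of GLP-1". No variance or effect size is given for any gene.

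**The concern.** Ct values are counts of doublings, so ΔCt and ΔΔCt are already on a log2 scale. Raising 2 to the power -ΔΔCt undoes that logarithm. If ΔΔCt is roughly symmetric between participants, fold change has a long right tail. Three things follow for these primary outcomes:

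1. The arithmetic mean sits above the typical (geometric mean) fold change, and a few large values drive the SD.
2. Methods that compare arithmetic means lose power.
3. An adjusted difference in fold changes is harder to interpret than a ratio.

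The question is how much of this survives the plan's own normality check and rank-test route.

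**Working it through.** **Inputs.** From the article: "two-sided *α* = 0.05 and *β* = 0.2"; "Δμ = 17.84; SD1 = 17.93; and SD2 = 22.49" for GLP-1; and "considering a 20% dropout rate, 25 subjects were calculated for each group". Assumed, because the article does not give them: SD of ΔΔCt from 0.5 to 2.0 cycles, normal ΔΔCt, one exponentiated value per participant, and a correlation of 0.5 between baseline and end ΔCt.

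**Step 1. The plan's own figure.** n = (1.960 + 0.842)² × (17.93² + 22.49²) / 17.84² = 7.849 × 827.28 / 318.27 = 20.40 per arm. Multiplying by 1.2 gives 24.5, rounded up to 25. The stated size reproduces. It rests on GLP-1 and does not bear on the gene scale. It does set the number to work with: 25 × 0.8 = 20 per arm after dropout.

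**Step 2. Mean against typical value.** For lognormal fold change, arithmetic mean / geometric mean = exp[(ln 2 × SD)² / 2]:

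| SD of ΔΔCt (assumed) | (ln 2 × SD)² / 2 | Ratio |
|---|---|---|
| 0.5 | 0.060 | 1.06 |
| 1.0 | 0.240 | 1.27 |
| 1.5 | 0.541 | 1.72 |
| 2.0 | 0.961 | 2.61 |

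With no change in either arm the geometric mean is 1, so these ratios are also the expected mean fold changes under no effect, the same in both arms.

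**Step 3. Unadjusted comparison.** Simulation: 3,000 trials per setting, 20 per arm, effect set to give 80% power for a t-test on ΔΔCt. In the gated columns Mann-Whitney replaces the t-test if either arm fails the normality test.

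| SD | t-test on ΔΔCt | Raw t-test, no gate | Mann-Whitney | Plain KS rejects | Gated, plain KS | Gated, Lilliefors |
|---|---|---|---|---|---|---|
| 0.5 | 82% | 79% | 80% | 1% | 79% | 81% |
| 1.0 | 81% | 71% | 78% | 11% | 74% | 78% |
| 1.5 | 80% | 60% | 78% | 37% | 74% | 78% |
| 2.0 | 79% | 46% | 76% | 71% | 75% | 76% |

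The gated loss is therefore a few points; a repeat simulation put gated power at about 74% to 78%. Over runs with 20 and 25 per arm, type I error of the raw t-test was 3.5% to 5.3%.

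**Step 4. Baseline-adjusted comparison.** With equal SDs σ of ΔCt at both visits and correlation 0.5, Var(ΔΔCt) = 2σ²(1 − 0.5) = σ². The residual SD in ΔCt ANCOVA is σ√(1 − 0.5²) = 0.866σ. The effect from Step 3 is 0.91σ, so the standardised effect is 0.91 / 0.866 = 1.05, whatever σ is. Simulated power is about 89%. On the raw scale, by simulation:

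| SD | ΔCt ANCOVA | Raw-scale ANCOVA | Loss (points) |
|---|---|---|---|
| 0.5 | about 89% | about 87% | 2 |
| 1.0 | about 89% | about 77% | 12 |
| 1.5 | about 89% | about 63% | 26 |
| 2.0 | about 89% | about 46% | 43 |

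The article does not say which raw value enters as response. Modelling fold change, or end 2^-ΔCt, on baseline 2^-ΔCt gives much the same answer: 86–87%, 75–79%, 62–66% and 47–50%.

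**The case against.** The plan does not prescribe an unconditional t-test. Skewed variables go to rank tests, which a log transformation leaves unchanged, and the check fires most often where the raw t-test is worst. A reader might infer from the ungated column that the planned gene comparison has only 71%, 60% or 46% power at SDs of 1.0, 1.5 and 2.0. The article does not support that, because it describes the gated procedure. This part of the objection stands in full.

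A reader might also infer that the gene results will be biased upwards or prone to false positives. That is not supported either. The sample mean is an unbiased estimate of the arithmetic mean; it simply differs from the geometric mean. Under no effect both arms are raised equally, and the simulations show no inflation of type I error.

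Further, the size depends on an SD that the article does not give. At 0.5 cycle almost nothing is lost.

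Last, the article says how fold change is calculated but not whether tests run on 2^-ΔΔCt or ΔCt, nor whether exponentiation is per participant, and a full analysis plan could settle this. That lowers certainty. However, the Outcomes section names fold change itself as the primary quantity, and the Statistical analysis section applies mean ± SD and ANCOVA without naming another scale. The point is therefore about a stated choice and not about a detail left out.

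None of this reaches the two places that the normality check does not cover: the mean ± SD summary and the ANCOVA.

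**Conclusion.** The concern holds in a limited form. Fold change is a poor scale for summarising and baseline-adjusting the three primary gene outcomes. Reported means would exceed the typical fold change by 6% to 161% for SDs of 0.5 to 2.0 cycles. Raw-scale ANCOVA would lose from about 2 to about 43 points of power against ΔCt ANCOVA. In the unadjusted comparison the loss is only a few points, because of the rank-test route. Validity under the null is not in question.

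These sizes assume roughly normal ΔΔCt, per-participant exponentiation, 20 per arm and, for the ANCOVA, a baseline-to-end correlation of 0.5. The direction depends only on fold change being right-skewed. This is an improvement that should be made, not a flaw that invalidates the trial.

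**What to change.** In the Statistical analysis section, state for each gene:

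- The primary analysis is ANCOVA of end-of-study ΔCt on arm, baseline ΔCt, age group and sex, the last two being the stratification factors in the Blinding and randomization section.
- The adjusted arm difference d is reported as 2^-d, a ratio of geometric means, with its 95% CI back-transformed in the same way.
- Per-participant 2^-ΔΔCt is used for display only, and geometric means replace mean ± SD for gene expression.

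The wording should be fixed before the data are analysed. The cost is analysis wording only: assays, samples, visits and sample size are unchanged.

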### Outcomes

Primary outcomes will be changes in means of anthropometrics indices, serum levels of GLP1, and fold change of PGC-1α, PPARα, and UCP1 genes between the control and intervention groups. Secondary outcomes are to compare the changes in means of lipid profile (serum levels of TG, TC, HDL-C, and LDL-C), FBS, fasting plasma insulin level, HOMA-IR, ALT, AST, and ALP between the control and intervention groups. All primary and secondary outcomes will be evaluated at the baseline and the end of the study (day 60 after intervention) for all participants. All outcomes and time points are specified in Fig. 3.

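### The protocol names 5 to 14 unranked primary outcomes, each judged at P<0.05, while the sample size covers GLP-1 alone: the chance of at least one false-positive primary is about 23% to 51%, not 5%

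*Protocol article*

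**What the plan says.** All references are to the protocol article.

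- **Outcomes** gives the primary set: "Primary outcomes will be changes in means of anthropometrics indices, serum levels of GLP1, and fold change of PGC-1α, PPARα, and UCP1 genes". No outcome is put first, and the anthropometric indices appear only as a class.
- **Anthropometric assessments** describes what is measured. It covers body weight and then BMI ("To calculate BMI, weight (kg) will be divided by height squared"), waist ("An accurate measurement of waist circumference (WC) will be taken"), hip ("Hip circumference (HC) will be measured at its widest point") and their ratio ("Waist/hip ratio (WHR) will also be calculated"). The body composition analyzer adds five more: "Fat-free mass (FFM), FFM percent, fat-mass (FM), and FM percent, as well as visceral fat". That makes ten.
- **Statistical analysis** compares the arms on every primary and secondary outcome, with one criterion: a P-value "less than 0.05 will be considered a statistically significant".
- **Sample size**: "The sample size was estimated based on serum changes of GLP-1". The inputs are a difference of 17.84, SDs of 17.93 and 22.49, two-sided alpha 0.05, 80% power and 20% dropout, giving 25 per arm. No other outcome is sized.

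**The concern.** A trial with several primary outcomes needs a rule linking the individual tests to its conclusion. Here the article fixes the list and the threshold for each test, but not that rule. A reader of the final report could then meet one significant primary among many and take it as a positive superiority trial with a 5% error rate. That rate holds for each test taken alone, not for the set. The stated 80% power has the same limit: it describes GLP-1 tested alone at 0.05 and says nothing about the gene or anthropometric primaries.

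**Working it through.** **1. Reproduce the sample size.**

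The two-means formula is n per arm = (1.960 + 0.842)² × (SD1² + SD2²) / difference².

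- SD1² + SD2² = 17.93² + 22.49² = 321.48 + 505.80 = 827.28.
- Difference² = 17.84² = 318.27.
- n = 7.849 × 827.28 / 318.27 = 20.4 evaluable per arm.
- With dropout: 20/0.8 = 25; 20.4/0.8 = 25.5; 20.4 × 1.2 = 24.5.

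The stated 25 per arm is reproduced within rounding, for GLP-1 only and at an unadjusted 0.05.

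**2. Count the primaries.**

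| Reading of the anthropometric class | Indices | Plus GLP-1 and 3 genes |
|---|---|---|
| One index or one domain | 1 | 5 |
| Weight, BMI, waist, hip, waist/hip ratio | 5 | 9 |
| All measures, less two near-duplicates | 8 | 12 |
| All measures described | 10 | 14 |

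The near-duplicates are BMI, which is weight over a fixed height squared, and fat-free mass percent, which is close to 100 minus fat mass percent.

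**3. Chance of at least one P<0.05 with no true effect, tests independent.** The formula is 1 − 0.95^k.

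- k = 5: 22.6%
- k = 9: 37.0%
- k = 12: 46.0%
- k = 14: 51.2%

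**4. The same chance with correlated indices.** The article gives no correlations, so these are assumptions: a common correlation among the anthropometric indices, 0.3 among the genes, and GLP-1 independent of both. Simulated under a multivariate normal null:

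| Correlation among indices | 10 indices (14 primaries) | 8 indices (12 primaries) |
|---|---|---|
| 0.3 | 47% | 42% |
| 0.5 | 41% | 38% |
| 0.7 | 35% | 34% |
| 0.9 | 28% | 28% |

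Correlation lowers the figure, but it stays at more than five times the nominal 5%.

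**5. GLP-1 power under adjustment.** The standardized difference is 17.84 / √(827.28/2) = 17.84 / 20.34 = 0.877. With 25 per arm and 20% dropout, 20 per arm are evaluable. Two-sample t-test power is then:

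- alpha 0.05: 77% (79% by the normal approximation)
- alpha 0.05/5 = 0.01, the strictest Holm step for five primaries: 53%
- alpha 0.05/14 = 0.0036: 38%

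The present size supports GLP-1 as a single primary at close to the intended power. It does not support GLP-1 as one of many adjusted primaries.

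The figures take one test per outcome. The t-test, rank test, covariance analysis and percentage change that the article also mentions could raise the error further and are not included.

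**The case against.** **The count of 14 is inferred.** This stands. The Outcomes section does not list the indices and refers to Figure 3, which is not shown. Fourteen is the upper reading, so a range is given. The lowest reading still has five primaries and an error rate of about 23%.

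**A false-positive primary is not shown to be more likely than not.** This also stands. A reader might infer from the 51% that a chance finding is the expected result. That needs fourteen independent tests, and body-size measures are plainly not independent. Every correlated scenario above is below 50%.

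**No rule says that one significant result makes the trial positive.** True. A reader might take the outcomes as co-primary in the strict sense, where all must succeed and the error rate is not inflated, or might assume that any one suffices. The article states neither. The figures describe what happens if any one is accepted, which nothing in the article prevents.

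**A separate analysis plan could hold an adjustment.** It could, and this review does not claim that none exists. But the primary list, the 0.05 threshold and the sample size are all stated here. An adjustment made elsewhere would leave GLP-1 with less power than the Sample size section states.

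**The trial is groundwork for larger studies.** The Discussion does look ahead to multi-center trials, but the Study design section calls this a superiority trial. Modest aims soften the consequences; they do not restore the 5%.

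**Conclusion.** The point holds as a finding about multiple unranked primaries. As written, the chance of at least one nominally significant primary under no effect is roughly 23% to 51%, or about 4.5 to 10 times the nominal 5%. For 14 primaries with assumed correlations of 0.3 to 0.9 among the indices it is about 47% down to 28%. The ends of the wider range depend on how many indices count as primary and on independence; the middle depends on correlations that the article does not give. The stated 80% power is reproduced within rounding and applies to GLP-1 only. The defect matters because it determines what the trial may conclude.

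**What to change.** The article does not show whether the data are still blinded. Recruitment was expected to end in November 2021 and the article is dated August 2023. The fix depends on that.

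- **If still blinded, one primary.** Name it by amendment before unblinding. Change in serum GLP-1 is the choice consistent with the Sample size section: 25 per arm and two-sided 0.05 then stay coherent. The gene and anthropometric outcomes become secondary, reported as estimates with 95% confidence intervals.
- **If still blinded, a short primary set.** Where GLP-1 alone is not acceptable scientifically, list the primaries explicitly (for example GLP-1, one named anthropometric index and the three genes), test them with Holm and restate the power. For GLP-1 at 20 evaluable per arm that means 77% at 0.05 and about 53% at the strictest step of 0.01.
- **If already unblinded.** Do not change the primary, since that would be outcome switching. Report all listed primaries with Holm-adjusted P-values and disclose the multiplicity.

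The first two options need a protocol and registry amendment, for which the Registries and ethics section already provides a route. None needs more patients or data. The cost is fewer outcomes that can support a primary claim, or a lower stated power.
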